### Phase 2: intervention

Similar to phase 1, 10 elementary schools will randomly be selected from five districts of Tehran. The mothers of children from these schools will be recruited to assess the effect of the new label. To invite the participants, the mothers will be contacted by phone, until 50 literate mothers accept to cooperate. After obtaining informed consent, demographic data will be collected and mothers will be asked to complete the International Physical Activity Questionnaire (IPA) [27] in order to determine whether they have any especial interest in physical activity that may affect their attention to physical activity calorie equivalent labeling. Five hundred mothers will be randomly assigned to enter the study and each 100 one of them will go to one of the five groups. No relevant information regarding use of food labels will be given to mothers, except for two groups. The study groups will be as follows: (1) without nutrition label group, (2) current traffic light label group, (3) physical activity calorie equivalent label group, (4) current traffic light label group with a brochure for more information, and (5) physical activity calorie equivalent label group with a brochure for more information. A “food choice” brochure will be handed to mothers describing the labeling information in detail and the participants will be asked to read it after filling their questionnaires.

We will present products of each groups in one classroom and so, we will have 3 classrooms for participants. The first classroom will include food items “without nutrition label”, the second classroom will be for “current traffic light label” and “current traffic light label group with a brochure for more information” and finally the last classroom will be presented by foods with “physical activity calorie equivalent label” and “physical activity calorie equivalent label group with a brochure”. Milk, yogurt and cheese will be in the dairy group. Due to different brands designs, there will be at least 30 dairy products. Twenty beverages and twenty cakes and biscuits will be shown in other rows. All the foods in five food groups will be similar in brand and type.

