Products included in the “without nutrition label” group will provide no nutrition information. There will be no change in the traffic light label group and the labels will appear exactly as produced by factories. Calories and serving sizes of products on labels will be based on factories definition and we do not change them. Each particular food with either no label, or old traffic light label, or our newly designed label will be presented into 3 classrooms similarly. Groups in traffic light label and physical activity calorie equivalent label will only be different in the form of figures and presentation of some information such as physical activity. Finally, the products with physical activity calorie equivalent labels will be covered with the new designed label. Each mother will be asked to imagine she is in a supermarket, choose one product that she wants from each category to buy for her family; place them in a bag inside the room, and then leave there. One of the researchers will record food items. For example, one package of creamy cake has about 320 cal, while there is another cake with only 130 cal; so we expect mothers to choose better option based on the information provided by the labels. Thus, at the end of the study, the total calories from each category as well as the total calories of all selected foods will be compared among different 5 groups. For each of the five groups, the “time” spent by each participant while selecting food items will be recorded by the researcher. After the food choice stage, a series of short questions will be asked in order to assess the mothers’ attention to the mentioned labels. All the collected data will be entered into a database.

Accordingly, the major consequence obtained in this step will show the effect of the new designed label that focuses on the differences in calories for each food group. Accordingly, the major consequence obtains from this step would be the effect of the new label on choosing lower calories goods by consumers and the second outcome would be the time spent while food selection according to different labels.

#### Randomization method in phase 2

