Stratified balanced blocked randomization will be applied. Strata are schools, and each of the five blocks consists of ten participants in every school. The blocks and sequence within block will be generated using the Stata Statistical Software and will be given to the person who will manage random allocation of individuals in the school. This method will balance the number of participants in all groups and ensure allocation concealment. The assessor and the analyzer will be blind to groups’ randomization and outcome evaluation.

Mothers will be selected by a person other than the investigator. On the other hand, mothers will select food products while they are alone in the room. The diagram of the intervention phase and the time schedule are shown in Figs. 1 and 2, respectively.

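### The plan states that the assessor is blind, but as described whoever records the foods and the selection time cannot be blind to label type

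*Protocol article*

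**What the plan says.** Under *Randomization method in phase 2* the article states that "The assessor and the analyzer will be blind to" both the allocation and the outcome evaluation. It does not say who the assessor is. The same section adds that "mothers will select food products while they are alone in the room".

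Under *Phase 2: intervention* the procedure is as follows.

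- **Rooms.** "We will present products of each groups in one classroom and so, we will have 3 classrooms for participants". One room holds products without nutrition information. One holds products with the factory traffic light label and serves the two traffic light arms (with and without brochure). One holds products with the activity label and serves the two activity label arms (with and without brochure).
- **Packs.** The condition is on the product itself. In the third room, for example, "the products with physical activity calorie equivalent labels will be covered with the new designed label".
- **Foods.** The mother is to "place them in a bag inside the room, and then leave there". Then "One of the researchers will record food items".
- **Time.** In each of the five groups, the time "spent by each participant while selecting food items will be recorded by the researcher".
- **Questions.** After the choice, mothers answer short questions on their attention to the labels. The article does not say who asks them.

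**The concern.** The blinding sentence is an affirmative claim, and the procedure in the preceding section appears to contradict it. The only people described as capturing outcomes are researchers. They take the foods from a bag of labelled packs left in a room tied to one label condition, and they time a mother's stay in such a room.

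If the sentence stands, a reader will credit the label comparisons with a protection against recorder bias that the procedure does not give. Those comparisons, above all activity label against traffic light, are what the trial is for. The matter is most relevant to selection time, the second outcome, where the recorder may influence the value, and to the label-attention questions if the recorder asks them.

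**Working it through.** The article attaches no figure to blinding, and the sample size does not depend on it. The check is to map arms to rooms and ask what the recorder can know.

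**Inputs** (*Phase 2: intervention*): five arms of 100 mothers, 500 in total; three rooms.

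| Room | Arms | Mothers |
|---|---|---|
| No label | N | 100 |
| Traffic light | T, T + brochure | 200 |
| Activity label | P, P + brochure | 200 |

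**Step 1: what the room or the pack reveals.** In the no-label room the arm is fully identified: 100 of 500 mothers. For the other 400 it is narrowed to two arms that differ only by brochure.

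- Chance of naming the arm without room or pack: 1/5 = 20%.
- Chance knowing the room, with a random guess on brochure: (100/500) × 1 + (400/500) × 1/2 = 0.20 + 0.40 = 60%.

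**Step 2: which contrasts are open.** Five arms give 5 × 4 / 2 = 10 pairwise contrasts. Those within a room are T against T + brochure and P against P + brochure, so 2. The other 10 − 2 = 8 are between rooms, and in each of these the recorder can see the difference being tested. All contrasts of one label type with another, or with no label, are among the 8.

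**Step 3: which outcomes are exposed.**

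- *Energy of the chosen products.* One product is chosen per category and calories follow the manufacturers' definitions. The recorder notes which product is in the bag, with little room for judgement. Exposure is small.
- *Selection time.* The value depends on when the recorder takes selection to begin and end. Exposure is larger.
- *Label-attention questions.* Exposed if the person asking knows the label type.

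**Step 4: recorder and room.** Write a recorded time as true time plus a recorder offset d. If recorder A stays with one room and recorder B with another, the expected difference between the rooms is the true label difference + (d_A − d_B), and the data cannot separate the two terms. The article gives no staffing pattern, so this is conditional.

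Now suppose three recorders, one per room in each school, all three rooms set up in each school, and a cyclic rota. The 10 schools of 50 mothers give three full cycles (9 schools) plus one. Offsets cancel over the 9 schools and remain in the tenth, with weight 50/500 = 1/10, leaving (d_A − d_B)/10. A recorder term in the model would deal with that remainder.

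**The case against.** The strongest reply is that the article does not define the assessor. The same foods are shown in all three rooms, so a list of product names need not reveal the label, and a separate person who assigned energy values from such a list could truly be blind. That reading is possible. On it, however, the sentence describes someone downstream of the measurement and gives no protection where foods and times are captured. The claim would still need that limit stated.

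Second, mothers choose alone, so a reader who infers that the researcher works inside the labelled classroom goes beyond the text. This stands, but it does not restore blinding: the bag still holds labelled packs, and the person timing still has to know which room the mother is in.

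Third, a reader might infer that blinding is impossible altogether. The article does not support that. The analyst can work with coded arms. Brochure status can be kept from the recorder, because both arms of a label share a room, provided that someone else hands out the brochure.

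Fourth, nothing says that time is taken by hand or that each recorder keeps to one room. A condensed article may also leave timing rules and staffing to the full protocol. This too stands: the absence of those details is not the fault here, and the confounding in Step 4 is a possibility, not a feature of the plan.

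**Conclusion.** The unqualified statement that the assessor is blind cannot be reconciled with the described procedure for label type if the assessor is whoever records foods or time, and no other outcome assessor appears in the article. In size, 8 of 10 pairwise contrasts are open to the recorder, the no-label arm is fully identified, and only the 2 brochure contrasts can be masked from that person.

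The consequence is limited. It would be tempting to infer that the primary comparison of calories is biased, but identifying a product in a bag leaves little discretion, and nothing in the article suggests material error there. The exposed outcomes are selection time and, conditionally, the label-attention questions. No amount of bias can be put on either from the document. Full confounding of recorder with label rests on the assumption that each recorder stays with one room, which is not stated.

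This is a false assurance to be corrected, with a modest design safeguard for the secondary outcome. It is not a defect that undermines the trial.

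**What to change.** 1. Say who the assessor is, and restate blinding: the analyst is blind to coded arms; the person recording foods and time is blind to brochure status only and is not blind to label type. Have someone other than the recorder hand out the brochures.
2. Define selection time as room entry to room exit, logged with a timestamp, so that the recorder's judgement does not enter.
3. If more than one recorder is used, rotate them across the three rooms from school to school on a schedule set in advance, and keep the recorder's code in the data set.
4. Say who asks the label-attention questions, and report them as unblinded if that person knows the label type.

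The cost is some rewording, a timing rule and a simple rota. Arms, sample size and the main analysis do not change. Staffing is not described, so whether the rota needs any rearrangement is for the investigators to judge. The drawback is a weaker blinding statement, but one that the procedure supports.

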**Fig. 1 Fig1:**
[figure not shown]
participants’ flow diagram (phase 2)

**Fig. 2 Fig2:**
[figure not shown]
The schedule of enrolment, interventions, and assessments of participants in phase 2

### Selection criteria

Participants will be literate mothers who are willing to participate in the study. The mothers who are nutritionist or food technologist will not be included.The age of students will be 6–12 years. However, we will put no limitation for age of mothers who will enroll the study.

### Phase 1

FGDs will consist of 6 to 10 people and at least 6 industrialists and experts will be interview, and will continue until data saturation is achieved.

### Phase 2

#### Method of calculating sample size and number

We calculated the number of participants by using G*Power software 3.1 [28]. In this regard power analysis was applied based on a linear multiple regressions with an assumed small to medium effect size (f = 0.18). The total sample size in this case will be 481 with power of 0.9. The sample size is 96 in each arm after attrition, and we scaled that up to *n* = 100 therefore, 500 subjects will be studied in total. Due to the multiple comparisons, alpha level will be adjusted and interpretation of statistically significant results will be done by taking conservative cautions.

#### Qualitative analysis of data in phase 1

The MAXQDA 10 software will be used to analyze the interviews. This software is used to analyze social-oriented texts [29]. Qualitative analysis with thematic approach will be used. It will be done as follow. First, data will be analyzed after each group discussion or interview; for this purpose, all the data will be entered into the software in a textual format. The strengths, weaknesses, description, and information for the new physical activity calorie equivalent label will be defined as categories, and each category will be stored in a special part of the software. Thereafter, decision will be made on coding units after reading the text for several times and the codes will be added to each relevant category at the same page of the software. At this point, classification will be done using the data of the study, and the stability of the coding will be tested. The coding stability will be re-checked after encoding the full text in the software. Finally, the structures of meanings will be provided based on the data inference.

#### Statistical analysis of data in phase 2

Analysis of Variance (ANOVA) will be used to examine the relationship between the label type and the main consequence showing calorie of the selected products and the second outcome which is spent time during food selection. The purpose of this analysis is to see whether the difference between different groups has a significant effect on the main outcome. In order to adjust the effect of confounders (education level, body mass index, age, and socioeconomic status) multiple linear regressions will be used and the energy of the selected food products in each group will be analyzed. In all tests, type I error will be considered 5% and the data will be analyzed using the Stata 12 and SPSS version 16.

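### Randomisation is stratified by school, but school is in neither the ANOVA nor the adjusted regression, so the ANOVA is somewhat conservative and gives up a little precision

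*Protocol article*

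**What the plan says.** Under the heading Phase 2: intervention, the Protocol article says that "10 elementary schools will randomly be selected from five districts of Tehran", and that "the mothers will be contacted by phone, until 50 literate mothers accept to cooperate". Allocation is of individual mothers: "Five hundred mothers will be randomly assigned to enter the study and each 100 one of them will go to one of the five groups".

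Under the heading Randomization method in phase 2: "Stratified balanced blocked randomization will be applied" and "Strata are schools, and each of the five blocks consists of ten participants in every school". Five blocks of ten make 50 mothers per school, and ten schools make 500. With five arms in balance, that is 10 mothers per arm in every school.

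Under the heading Statistical analysis of data in phase 2, ANOVA relates label type to the energy of the chosen products and to the time taken. The adjusted analysis is then given with its covariates named: "In order to adjust the effect of confounders (education level, body mass index, age, and socioeconomic status) multiple linear regressions will be used". Type I error is set at 5%. No section adds school to either model.

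The article also has every mother complete the physical activity questionnaire (IPAQ) at baseline, to learn "whether they have any especial interest in physical activity that may affect their attention to physical activity calorie equivalent labeling". IPAQ is not in the covariate list.

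**The concern.** Once allocation is balanced within school, differences between schools cancel out of the arm comparisons. The estimates are therefore more precise than a simple comparison of five unstructured groups would suggest. An analysis that leaves school out does not know this. It counts school-to-school variation as noise, reports standard errors that are too large for the design, and tests at less than its nominal 5%.

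Some variation between schools is plausible here, because they are drawn from five districts across the city. What is at stake is precision and a little power, given up for no return. The balance was paid for at randomisation and is not collected at analysis.

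**Working it through.** **Inputs from the article.** 10 schools; 5 blocks of 10 per school; 5 arms of 100; f = 0.18; planned power 0.90; N = 481, rounded up to 500; alpha 0.05.

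**Assumed.** The school ICC is not given, so a range of 0.02, 0.05 and 0.10 is used, with total variance set to 1. The number 50 is read as 50 mothers per school, which is the only reading that agrees with five blocks of ten and a total of 500.

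**1. The plan's own figure.** A 4-degree-of-freedom F test with noncentrality N × f² and f² = 0.18² = 0.0324 has power 0.8998 at N = 480 and 0.9005 at N = 481. The stated 481 is reproduced. At N = 500 the power is 0.913. This calculation contains no school effect.

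**2. Variance of an arm difference.** With exact balance, the true sampling variance depends only on the within-school part, 1 − ICC. Without a school term, each arm's within-arm sum of squares picks up an expected 10 × 9 × ICC = 90 × ICC from schools, or 450 × ICC over five arms, on 495 degrees of freedom. The model variance divided by the true variance is therefore

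1 + (450/495) × ICC/(1 − ICC)

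| ICC | Variance ratio | SE ratio (square root) |
|---|---|---|
| 0.02 | 1.019 | 1.009 |
| 0.05 | 1.048 | 1.024 |
| 0.10 | 1.101 | 1.049 |

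The variance is overstated by about 2% to 10%, and the standard error by about 1% to 5%.

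**3. Type I error and power of the omnibus test.** Without school, the F statistic is shrunk by roughly the ratio above, so the effective critical value is 2.39 × ratio. With school, the noncentrality is 500 × 0.0324/(1 − ICC) = 16.53, 17.05 and 18.00, on 4 and 486 degrees of freedom.

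| ICC | Type I error, no school | Power, no school | Power, with school | Gain (points) |
|---|---|---|---|---|
| 0.02 | 4.7% | 0.914 | 0.919 | 0.5 |
| 0.05 | 4.2% | 0.916 | 0.927 | 1.1 |
| 0.10 | 3.4% | 0.919 | 0.941 | 2.2 |

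Simulation of 10 schools × 5 arms × 10 mothers agrees to within a few tenths of a point: type I error of about 4.3%, 4.0% and 3.3% without school, and power without versus with school of 0.912 vs 0.916, 0.918 vs 0.929 and 0.919 vs 0.940. With school in the model, simulated type I error stays near 5% (4.7% to 5.1%).

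The two powers must be compared at the same ICC. Setting the with-school figures against 0.913, which is the value at ICC 0, would overstate the gain.

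**4. IPAQ, for contrast.** IPAQ is not a stratification factor. In simulations where it explains 2% to 10% of the variance (assumed), the ANOVA without it keeps a type I error of 4.7% to 5.2%, and its model standard error agrees with the true one. Leaving IPAQ out may cost some precision, but the standard errors stay valid.

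**The case against.** **The effect is small and on the safe side.** This stands. Estimates are unbiased, false positives are not inflated, and power at 500 stays above the planned 0.90 at every ICC considered. At ICC 0 nothing is lost.

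**The adjusted regression already recovers part of it.** This also stands. If schools differ mainly in social composition, education and socioeconomic status take up part of the between-school variance. The figures above describe the ANOVA. The loss in the regression is smaller, by an amount that cannot be computed from the article.

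**A condensed article may leave stratum terms to an analysis plan.** This stands only in part. The list is headed as confounders, and a design stratum is not a confounder, so the list need not be read as exhaustive. But the article does set out both models, names the covariates of one, and omits the only factor used in randomisation.

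**A reader might infer that omitting IPAQ also makes the standard errors wrong, or that its purpose is wholly unserved.** The article does not support either. IPAQ did not enter the randomisation, so the analysis is valid without it. The stated purpose, "in order to determine whether they have any especial interest in physical activity that may affect their attention to physical activity calorie equivalent labeling", commits to no covariate or interaction, and describing the arms at baseline could meet it.

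**A reader might also infer that mothers within schools call for a cluster design effect and a larger sample.** They do not. Mothers are randomised individually within school, so between-school variance cancels from the comparisons. Ignoring school makes the test conservative, not liberal.

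**Conclusion.** The point holds for school. The article stratifies by school and states two analyses without it. In the ANOVA this overstates the variance of arm differences by about 2% to 10%, takes the type I error of the omnibus test down to about 4.5% to 3.3%, and forgoes about 0.4 to 2 points of power at f = 0.18 and N = 500. These figures rest on an assumed ICC of 0.02 to 0.10 and on 10 mothers per arm in each school. The loss is nil at ICC 0 and smaller in the covariate-adjusted regression.

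This is a mismatch of design and analysis that costs some precision. It does not threaten the validity of the trial's conclusions, and it gives no reason to change the sample size. It is worth correcting because the correction is almost free.

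**What to change.** State that school enters as a ten-level fixed effect in the primary model for energy and in the model for time, both in the ANOVA and in the regression adjusted for education, body mass index, age and socioeconomic status. The cost is a line of wording and 9 degrees of freedom (495 to 486 residual in the ANOVA). No new data are needed, and the sample size stays as it is.

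Separately and optionally, IPAQ could be used in one prespecified exploratory interaction with label type, since the stated reason for collecting it is that activity interest may affect attention to the activity label.

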**Methods:**

This study will be conducted in two phases. In phase 1, nutrition fact labels and traffic light labels will be assessed through focus group discussions and interviews among different groups of mothers, industrialists and nutrition and food industry specialists as to determine strengths and weaknesses of the current labels on packaged products. Then, the initial layout of the physical activity calorie equivalent label will be drawn with respect to the viewpoints received from mothers. Thereafter, we will include the scientific opinions to it for creating the first draft of our new label. In phase 2, a total of 500 mothers of students 6–12 years old randomly assigned to five groups. The study groups will be as follows: (1) without nutrition label group, (2) current traffic light label group, (3) current traffic light label group in which, a brochure will be used to inform mothers, (4) physical activity calorie equivalent label group, and (5) physical activity calorie equivalent label group in which a brochure will be used to inform mothers. Some samples of dairy products, beverages, cakes, and biscuits will be presented. ANOVA and multiple linear regressions will be used to examine the association between the label type and the main consequence (energy of the selected products) and secondary outcome (time).

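### The main outcome is tested by both an unadjusted ANOVA and an adjusted regression at 5%, and the text gives conflicting cues on which one decides

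*Protocol article*

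**What the plan says.** All of this stands in the Protocol article.

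- **Statistical analysis of data in phase 2, first model:** "Analysis of Variance (ANOVA) will be used to examine the relationship between the label type and the main consequence". Its aim is then given: "The purpose of this analysis is to see whether the difference between different groups has a significant effect on the main outcome".
- **Same section, second model:** in order to "adjust the effect of confounders (education level, body mass index, age, and socioeconomic status"), the article adds that "multiple linear regressions will be used and the energy of the selected food products in each group will be analyzed".
- **Same section, error rate:** "In all tests, type I error will be considered 5" per cent.
- **Abstract, Methods:** "ANOVA and multiple linear regressions will be used to examine the association between the label type and the main consequence". No order of importance is given.
- **Method of calculating sample size and number:** "power analysis was applied based on a linear multiple regressions with an assumed small to medium effect size" (f = 0.18), giving a total of 481 at power 0.9, raised to 500. The same paragraph says: "Due to the multiple comparisons, alpha level will be adjusted". It gives no method and no list of the tests covered.

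Neither model is called primary, supportive or a sensitivity analysis.

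**The concern.** Two models answer the same question about the same outcome, and both have the same 5% threshold. The text points both ways on which one counts. The analysis section ties the language of significance to the ANOVA. The sample-size section names regression as the model behind the power. The abstract lists the two as equals.

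The two F tests are highly correlated but not identical, so in a borderline trial one can fall below 0.05 and the other above it. The article then gives no basis for saying which result stands. Two things are at stake: a false-positive rate above the stated 5% if either result may be taken as the finding, and some lost power if the unadjusted test is taken as decisive although the covariates are collected and adjustment is already planned.

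This point is only about the model applied to one outcome. It does not concern which outcome or which pair of arms is primary.

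**Working it through.** **Inputs from the article.** Five arms of 100 (N = 500); f = 0.18, so f² = 0.0324; power 0.9; stated total 481; alpha 5%; four covariates. The article gives no covariate R² (share of outcome variance explained), so R² is an assumption and is varied.

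**Step 1: reproduce the stated total.** Noncentral F with λ = f²·N and 4 numerator degrees of freedom (5 arms − 1).
- N = 481: λ = 0.0324 × 481 = 15.58, power 0.9005. This is the smallest N that reaches 0.90, so the stated figure is reproduced.
- N = 500: λ = 16.2, power 0.913.

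**Step 2: does 481 reveal the model?** A one-way ANOVA gives 481. A regression testing the four arm terms, with 5 to 12 predictors in all, also gives 481. An overall regression test that counts every predictor would need 597 (8 predictors) to 685 (12). So 481 belongs to the 4-df label test at 5%, and that test exists in both models. The sample size does not settle which one decides.

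**Step 3: error rate if either test may decide.** Simulated data: 5 × 100 mothers, four covariates, no label effect, both 4-df F tests at 5% on the same data, 40,000 replicates per row (standard error about 0.1 point).

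| Assumed R² | ANOVA alone | Regression alone | Either |
|---|---|---|---|
| 2% | 5.1% | 5.2% | 5.9% |
| 5% | 5.0% | 5.0% | 6.2% |
| 10% | 5.0% | 5.0% | 6.6% |
| 20% | 5.0% | 5.0% | 7.3% |
| 30% | 5.0% | 4.8% | 7.6% |
| 50% | 5.0% | 5.1% | 8.6% |

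Smaller repeat runs gave 5.6% at R² = 2% and up to 7.9% at R² = 30%. Hence the rounded range of about 5.6% to 8% for R² of 2% to 30%. Two independent tests would give 1 − 0.95² = 9.75%.

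**Step 4: power and disagreement.** Same set-up with a true label effect, 5,000 replicates per row. Disagreement = 2 × P(either) − P(ANOVA) − P(regression). Example, f = 0.12 and R² = 10%: 2 × 0.6216 − 0.5330 − 0.5880 = 0.122.

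| True f | R² | ANOVA | Regression | Either | Disagree |
|---|---|---|---|---|---|
| 0.18 | 5% | 91.2% | 92.8% | 93.5% | 3.1% |
| 0.18 | 10% | 91.0% | 93.8% | 94.7% | 4.7% |
| 0.18 | 30% | 91.8% | 98.2% | 98.5% | 6.9% |
| 0.12 | 5% | 55.6% | 57.6% | 60.5% | 7.9% |
| 0.12 | 10% | 53.3% | 58.8% | 62.2% | 12.2% |
| 0.12 | 30% | 55.1% | 72.6% | 75.3% | 22.9% |

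Repeat runs with other arm-mean patterns and with R² down to 2% widen the disagreement to about 2% to 8% at f = 0.18 and about 5% to 23% at f = 0.12. The power gain has a simple source: adjustment raises λ from 16.2 to about 16.2/(1 − R²), for example 16.2/0.9 = 18.0 at R² = 10%.

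**Step 5: does the alpha sentence help?** It names no method or family and is not tied to the two models. It sits uneasily beside 5% in all tests, and 481 is reproduced only at an unadjusted 5%; at 2.5% the total would be 555. Even a working adjustment would not say which model decides.

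School was not in the simulated models.

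**The case against.** The best case for the plan has five parts.

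1. **Ranking models is often left to the analysis plan, and this is a condensed article.** An unadjusted result followed by an adjusted one is a common layout. Silence alone would be no finding. But the article commits to both tests, sets 5% for each and gives opposite cues, so the point is badly fixed in the text itself.
2. **The analysis section can be read as putting ANOVA first.** It is named first, covers both outcomes and carries the purpose sentence, while regression has the narrower task of adjustment. This is a fair reading and perhaps the natural one within that section. The sample-size section pulls the other way, though only weakly, since 481 fits both models. For the same reason, a reader cannot infer from the sample size that regression was meant to be primary.
3. **The article promises an alpha adjustment and cautious interpretation.** It does, and any account of the error rate must say so. As shown in step 5, the promise does not resolve the choice of model.
4. **The excess error is small and conditional.** This stands. It arises only if the analyst may take whichever test is significant, and the article nowhere says that. ANOVA alone also has power 0.913 at N = 500, above the target, so the design is not endangered.
5. **Naming either model would remove the excess.** Also true. The preference for the adjusted model rests on its power, not on the sample-size wording.

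One might also object to calling the covariates confounders in a randomised comparison. That is wording only, changes no result, and is not part of this point.

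**Conclusion.** The point holds in a limited form. The article gives two tests of the main outcome, each at 5%, with conflicting cues on which decides.

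If either may decide, type I error is about 5.6% to 8% for an assumed covariate R² of 2% to 30%. If the covariates explain almost nothing, little is at stake. The clearer cost is ambiguity: the tests give opposite verdicts in about 2% to 8% of trials at the planned effect and about 5% to 23% at f = 0.12, which is smaller than planned.

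A reader might infer that the false-positive rate nearly doubles, or that the plan licenses choosing the favourable result. The documents support neither. The tests share the same data and are highly correlated, so the excess is about 1 to 3 points and not the 9.75% of independent tests. The article leaves the choice open; it does not endorse selection.

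**What to change.** In Statistical analysis of data in phase 2, and briefly in the abstract, state that the deciding test of the main outcome is the 4-df label-arm effect from one pre-specified linear regression containing education level, body mass index, age, socioeconomic status and school. School belongs in the model because the Randomization method section makes it the stratum. State that the unadjusted ANOVA is reported as supportive and cannot overturn the adjusted result.

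The adjusted model is preferred because at f = 0.18 its power is about 0.92 to 0.98 over R² of 2% to 30%, against about 0.91 for the ANOVA.

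**Cost:** wording, plus a simple rule for missing covariate values so that all mothers stay in the deciding model. Ten schools use 9 degrees of freedom; with one column per covariate, 500 − 5 − 4 − 9 = 482 remain for error, and slightly fewer if education or socioeconomic status is categorical. The sample size is unchanged. Splitting alpha equally between the two models would cost more: at 2.5%, power at N = 500 falls from 0.913 to 0.860.
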